### 3.1.3 IL-20

IL-20 belongs to the IL-10 family, also including IL-19, IL-22, IL-24 and IL-26, IL-28A, IL-28B and IL-29, which have high secondary structural similarities. The amino acid identity between these cytokines is however low. Activated monocytes are the main production sites for IL-20, which exerts its action through two receptor dimers, i.e. IL-20R1/IL-20R2 (type I) and IL-22R1/IL-20R2 (type II). When these two receptor dimers aggregate, a signal transduction is initiated. Both the type I and type II receptor complexes have been detected in several tissues, such as epidermis, lungs, brain and glands, but have so far not been detectable directly in immune cells. In lesional skin from psoriatic subjects both type I and type II are expressed.

There is strong evidence that IL-20 is involved in the pathogenesis of psoriasis, and increased IL-20 messenger ribonucleic acid (mRNA) levels have been detected in lesional skin from psoriatic subjects, where the expression primarily is located to the basal and suprabasal keratinocytes. Recently, it was demonstrated that IL-20 expression is induced by proinflammatory stimuli, i.e. IL-1 $\beta$ , IL-6 and UVB radiation, and it was also discovered that recombinant IL-20 stimulates T-cell proliferation in cell cultures of purified human CD45RA+ T-cells. Furthermore, IL-20 seems to be necessary for amplifying and sustaining keratinocyte activation.

Overexpression of IL-20 in transgenic mice have been interpreted as a psoriasis-like phenotype of the skin, though histologically not including the inflammatory component of human psoriasis.

Other experiments performed in mice also clearly indicate IL-20 to be involved in the development of psoriasis. In a xenograft model where lesional psoriatic skin is transplanted on the back of SCID mice, Anti-IL-20 treatment with both polyclonal and monoclonal antibodies resulted in a partial resolution of psoriatic plaques, and a decrease in the semi-quantitative psoriasis scores compared to vehicle. Anti-IL-20 also prevented the induction of psoriasis in mice transplanted with non-lesional skin and injected with activated autologous peripheral blood mononuclear cells. Finally, treatment with recombinant hIL-20, induced psoriasis in transplanted non-lesional skin, injected with autologous non-activated PBMC (in-house data).

### 3.1.4 Trial drug

Novo Nordisk has produced a fully human Anti-IL-20 mAb, called 109-0012, which binds ( $K_D$   $3.1 \times 10^{-11}$  M) to and neutralises the pharmacological activity of human IL-20. 109-0012 is an IgG4 isotype, with high efficacy ( $EC_{50}$   $2.7 \times 10^{-10}$ ), which is chemically and physically stable and does not induce complement activation. It is expressed in the CHO-K1-SV line using the Lonza Glutamine Synthetase expression system and no animal components are used during the production. Preliminary results from toxicology studies in non-human primates and mice have raised no safety concerns so far (please see IB, 1st Edition and any updates hereof).

### 3.2 Rationale for the trial

The rationale for the use of 109-0012 in the treatment of psoriasis is based on several reports from the literature and from preclinical development (see [3.1.3](#)).

At present there exists no permanent cure for psoriasis. Current treatment options only have moderate effect, although recently introduced biologics, especially TNF- $\alpha$  blockers, have shown improved sustained efficacy with PASI75 scores around 60%. In addition, there are also subjects who are refractory to available treatments or have a waning effect over time, as well as a rather delayed time of onset of clinical response. Furthermore, many drugs have significant side effects such as serious infections and potential malignancies. Thus, there is a need for developing a tolerable, safe, convenient, fast-acting and effective drug, which could offer a sustained remission to subjects suffering from psoriasis.

The trial will be conducted in adherence to “Guideline on Requirement for First-in-Man Clinical Trials for High Risk Medicinal Products, 2007” and “Guideline on Clinical Investigations of Medicinal Products Indicated for the Treatment of Psoriasis, 2004”.

## 4 Objectives and endpoints

### 4.1 Objectives

#### Primary objective:

##### SD and MD dose-escalation phases

1. To assess the safety and tolerability of SD and MD of Anti-IL-20 (109-0012) 100 mg/vial, administered subcutaneously, at escalating dose levels.

##### MD expansion phase

1. To assess the preliminary efficacy (PASI, PGA, as well as VAS in subjects with psoriatic arthritis) of Anti-IL-20 (109-0012) 100 mg/vial at the maximum tolerated dose.

#### Secondary objectives:

##### SD and MD dose-escalation phases

1. To assess the preliminary efficacy (PASI, PGA and VAS in subjects with psoriatic arthritis) of Anti-IL-20 (109-0012) 100 mg/vial.
2. To assess the PK after dosing of Anti-IL-20 (109-0012) 100 mg/vial as SD and MD.
3. To explore PD and PG biomarkers of Anti-IL-20 (109-0012) 100 mg/vial and its effects on skin, vasculature, and the immune system.
4. To assess the immunogenicity of Anti-IL-20 (109-0012) 100 mg/vial (for the SD dose-escalation phase samples will only be analysed in case of safety concerns).

##### MD expansion phase

1. To assess the safety and tolerability of Anti-IL-20 (109-0012) 100 mg/vial.
2. To assess the PK after dosing of Anti-IL-20 (109-0012) 100 mg/vial as MD.
3. To explore PD and PG biomarkers of Anti-IL-20 (109-0012) 100 mg/vial and its effects on skin, vasculature, and the immune system.
4. To assess the immunogenicity of Anti-IL-20 (109-0012) 100 mg/vial.

## 4.2 Endpoints

### Primary endpoint:

#### SD and MD dose-escalation phases

1. The primary endpoint for safety will be observed toxicity assessed using the US National Cancer Institute common terminology criteria for adverse events version 3 (CTCAEv3). Dose limiting toxicities (DLT) will be recorded, and maximum tolerated dose (MTD) will be determined according to the criteria described in [12.1.1](#) and [12.1.2](#).

#### MD expansion phase

- The primary endpoint for efficacy is PASI (PASI75).

### Secondary endpoints:

#### SD and MD dose-escalation phases

1. Efficacy
  - PGA
  - PASI (PASI75)
  - For subjects with psoriatic arthritis, assessment of arthritis symptoms using VAS
2. Pharmacokinetics
  - Terminal serum half-life ( $t_{1/2}$ )
  - Maximum observed serum concentration ( $C_{max}$ )
  - Time to reach maximum serum concentration ( $t_{max}$ )
  - Accumulation index ( $R_{acc}$ )
  - Area under the serum concentration-time curve ( $AUC_{0-\tau}$ ,  $AUC_{0-t}$  and AUC)
3. Pharmacodynamic biomarker assessments
  - Serum levels of IL-20 and sCD25
  - Proteomic profiling of serum and plasma biomarkers, e.g. by multi-analyte profiling
4. Pharmacogenomic biomarker assessment
  - Gene expression analyses in whole blood samples by global transcriptome profiling and quantifiable reverse transcriptase polymerase chain reaction (qRT-PCR) of selected biomarkers related to 109-0012 effects.
5. Immunogenicity assessment

- Detection of antibodies against 109-0012 and if present neutralising activity will be measured.

## 6. Safety

In addition to the primary endpoint the following endpoints will be recorded as secondary safety endpoints:

- Vital signs (blood pressure, pulse and temperature)
- ECG
- Laboratory safety parameters of haematology, biochemistry, hormones, lipids and urinalysis
- Immunogenicity (antibodies to 109-0012)
- Physical examination

Pharmacodynamic and pharmacogenomic parameters will not be analysed during the ongoing trial.

## MD expansion phase

1. Safety will be evaluated and observed toxicity will be assessed using the US National Cancer Institute CTCAE version 3. Furthermore the following parameters will also be assessed:
  - Vital signs (blood pressure, pulse and temperature)
  - ECG
  - Laboratory safety parameters of haematology, biochemistry, hormones, lipids and urinalysis
  - Immunogenicity (antibodies to 109-0012)
  - Physical examination
2. The following parameters will be recorded as secondary efficacy endpoints:
  - PGA
  - For subjects with psoriatic arthritis, assessment of arthritis symptoms using VAS
  - Quality of life (QoL; DLQI)
3. Pharmacokinetics
  - Terminal serum half-life ( $t_{1/2}$ )
  - Maximum serum concentration ( $C_{max}$ )
  - Time to reach maximum serum concentration ( $t_{max}$ )
  - Accumulation index ( $R_{acc}$ )
  - Area under the concentration-time curve ( $AUC_{0-\tau}$ ,  $AUC_{0-t}$  and AUC)
4. Pharmacodynamic biomarker assessments

a) Serum/plasma samples:

- Serum levels of IL-20 and sCD25
- Proteomic profiling of serum and plasma biomarkers, e.g. by multi-analyte profiling

b) Skin biopsies:

- Histopathological scoring including assessment of epidermal thickness and proliferation, e.g. by hematoxylin & eosin (H&E), keratin 16, and Ki67 stain
- Exploratory assessment of 109-0012 effects on skin, vasculature, and immune system may include but not be limited to:
  - expression of IL-20 and IL-20 receptors
  - infiltrating leukocyte subsets, e.g. CD3, CD11c, and CD68
  - IL-20 signalling, e.g. phosphorylated signal transducer and activator of transcription 3 (pSTAT3)
  - angiogenesis, e.g. CD31 stain

Lesional 6 mm biopsies will be collected. Each biopsy will be split into two halves for cryo preservation.

5. Pharmacogenomic biomarker assessments

a) Blood samples:

- Gene expression analysis by global transcriptome profiling and qRT-PCR of selected biomarkers related to 109-0012 effects.
- Genotyping of IL-20 single nucleotide polymorphisms (SNP) haplotypes.

b) Skin biopsies:

- Gene expression analysis by global transcriptome profiling and qRT-PCR of selected biomarkers related to psoriasis and 109-0012 effects.

Lesional 3 mm skin biopsies will be collected and cryo preserved.

6. Immunogenicity assessment

- Detection of antibodies against 109-0012 , and if present neutralising activity will be measured.

7. QoL assessed by DLQI

Pharmacodynamic and pharmacogenomic parameters will not be analysed during the ongoing trial.

## 5 Trial design

### 5.1 Type of trial

This is an adaptive, randomised, multicentre, double-blind, placebo-controlled phase 1/2a trial, studying the safety and tolerability of different dose levels of SD and MD of Anti-IL-20 (109-0012) 100 mg/vial. The trial will be performed in subjects with moderate to severe stable plaque psoriasis, with or without psoriatic arthritis. The MD dose-escalation will be performed partly in parallel with the SD dose-escalation phase; the first dosing of the MD dose-escalation phase will start when the third dose level of the SD dose-escalation phase has been evaluated by the Study Safety Group.

Initiation of the MD expansion phase, at the maximum tolerated dose, will depend on results from the dose-escalation phases and it will only be initiated as long as there is an acceptable safety profile. There will also be the possibility to go directly into a phase 2 dose-finding trial, and refrain from the MD expansion phase. The decision whether or not to continue with the MD expansion phase will be taken based on unblinded safety and efficacy data.

#### **SD, dose-escalation phase**

A total of 24 subjects (18 receiving active treatment and 6 receiving placebo) will be included in the SD dose-escalation phase. Each of the six different dose cohorts (maximum dose of 3 mg/kg) will consist of four subjects; three receiving active treatment and one receiving placebo. Subjects will be followed until trial Week 16.

#### **MD, dose-escalation phase and MD expansion phase**

A total of 20 subjects (15 receiving active treatment and 5 receiving placebo) will be included in the MD dose-escalation phase. Each of the five different dose cohorts (maximum dose of 2 mg/kg) will consist of four subjects; three receiving active treatment and one receiving placebo.

In the MD expansion phase, a total of 39 subjects (26 receiving active treatment and 13 receiving placebo) will be included, at the maximum tolerated dose. Subjects are not allowed to have participated in the previous phases (SD and MD dose-escalation phases) of the trial. Number of visits, time points for visits, dosing intervals and number of repeated doses will be identical between the MD dose-escalation phase and the MD expansion phase. See Section [8.1.2](#).

During both the MD dose-escalation phase and the MD expansion phase, subjects will receive four repeated trial drug administrations (once every second week) and will be followed through trial Week 22.

#### **Time schedules**

The overall time schedules and the trial design is shown in

Figure 5–1. The expected trial duration for the SD and MD dose-escalation phase is approximately 19 months (77 weeks), and 9 months for the MD expansion phase.

[figure not shown]

**Figure 5–1 : Illustration of the concept of the FHD trial, showing the SD phase at six dose levels, the MD phase at five dose levels, and an MD expansion phase at one dose level.**

## 5.2 Rationale for trial design

A cautious approach is recommendable when starting FHD trials with biologics. If feasible, the dose should be selected based on calculations using the “minimal anticipated biological effect level (MABEL)” approach. Due to lack of preclinical in vivo models and predictive in vitro models this has not been possible. However, a low and presumed safe first single dose has been rationalised from the lack of toxicity in the toxicology studies at all dose levels, combined with simulated human pharmacokinetics of 109-0012 and resulting IL-20 serum concentrations.

All subjects in each dose cohort will be randomised and there will be a time interval of at least 24 hours between dosing of all subjects in each dose cohort of the SD dose-escalation phase. Subjects will be monitored at the research facility during the first 24 hours. Before continuing to the next dose level, safety data for all subjects through trial Day 15 as well as PK data for all subjects through trial Day 15 will be evaluated by the Study Safety Group (See Section [12.6](#)).

All four subjects in each dose cohort can be dosed on the same day during the MD dose-escalation phase. During the MD dose-escalation phase subjects will be monitored continuously for the first 8 hours after the first drug administration. The second dose should be administered on trial Day 15, the third dose on trial Day 29, and the fourth and last dose will be given on trial Day 43. Subjects will be monitored in-house at the research facility for 4 hours after the second, third and fourth dose.

The dose-escalation decision in the MD dose-escalation phase will be made based on safety data from all subjects obtained through trial Day 57, two weeks after the last dose, as well as PK data through trial Day 57. [Table 5-1](#) shows the proposed doses and dose intervals for the dose-escalation phases and the relative time points for starting each cohort.

The MD dose-escalation phase will be performed in parallel with the SD phase, but the first dose cohort of the MD dose-escalation phase will not commence until the third dose cohort of the SD phase has been evaluated by the Study Safety Group ([Table 5-1](#)). This means that the first accumulated multiple dose has been covered by the single doses already administered. This trial design is considered both safe and efficient.

This adaptive trial design has been chosen in order to increase the chances of finding the optimal dose level as early as possible, to save as much time as possible and not to use more patients than really needed.

Placebo will be used as control in order to distinguish any potential effects between the drug itself and other effects, not related to the trial drug itself. Furthermore, due to the fluctuating character of the disease, placebo is needed in order to ascertain sensitivity.

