## 5.4 Rationale for treatment

The trial drug is a protein and can therefore not be administered orally. A subcutaneous injection in the abdomen has been chosen as the most appropriate administration. During the trial, medical personnel will perform the injection. Due to risk for unblinding, the person performing the injection must be trial independent and not take part in any other trial related activities.

The first dose has been selected based on results from pre-clinical studies and biomodelling/simulation data. The expected dose range is between 0.01 mg/kg and 3 mg/kg during the SD phase, and between 0.05 mg/kg and 2 mg/kg during the MD dose-escalation phase. Initiation of the MD expansion phase, at the maximum tolerated dose, will depend on results from the dose-escalation phases and will be decided upon when the SD and MD dose-escalation phases have been completed. It will only be initiated as long as there is an acceptable safety profile. There will also be the possibility to go directly into a phase 2 dose-finding trial, and refrain from the MD expansion phase, provided there is an acceptable effect. The decision whether or not to continue with the MD expansion phase will be taken based on unblinded safety and efficacy data.

During the MD dose-escalation phase and the expansion phase four repeated doses, once every second week, will be investigated. This dosing interval is chosen with respect to the expected half-life of the trial drug and future dosing convenience for subjects.

The decision for dose-escalation will be taken by the Study Safety Group according to the instructions in [Table 5-2](#). Administration of Anti-IL-20 (109-0012) 100 mg/vial at the next dose level can only be initiated when the following criteria are met:

- Safety assessments and evaluations by the Study Safety Group through trial Day 15 for individual subjects in the current dose cohort of the SD dose-escalation phase, and through trial Day 57 of the MD dose-escalation phase.
- Evaluation of PK data by the Study Safety Group through trial Day 15 for individual subjects in the current dose cohort of the SD dose-escalation phase, and through trial Day 57 of the MD dose-escalation phase.

- The next dose level has been approved by the Study Safety Group. The Study Safety Group will also have the mandate to add another cohort other than for safety reasons, if relevant.

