| 1 of 4                                                                                   | Enter four subjects (3+1) at the same dose level as the current level where the toxicity event occurred.                                                                                                                                                                                                                                                                                                                                                                                                                                                                                                                        |
| 1 of 8                                                                                   | Enter four subjects (3+1) at the next dose level, according to Table 5–1 .                                                                                                                                                                                                                                                                                                                                                                                                                                                                                                                                      |
| ≥2                                                                                       | 
The dose-escalation will be stopped at this level, and no further increase of dose will occur. There will however be the possibility to add four (3+1) subjects at one or maximally two different dose levels between the current dose limiting level and the previous dose level.
 
 
• The maximum tolerated dose (MTD) is the highest dose level below the maximum administered dose (MAD) where none or 1 subjects experience a DLT.
 
• The maximum administered dose is the highest dose given in the trial.
 
• The maximal feasible dose is 3 mg/kg.
 
 |

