#### **6.4 Withdrawal criteria**

The subject may withdraw at will at any time.

The subject may be withdrawn from the trial at the discretion of the Investigator or the sponsor due to safety concerns, or if judged non-compliant with trial procedures.

A subject must be withdrawn if the following applies:

1. Non-compliance with protocol procedures
2. Drug limiting toxicity (DLT) or other serious or significant adverse event that warrants discontinuation in the opinion of the investigator
3. Sponsor closure of the trial
4. Withdrawal of informed consent

For the MD dose-escalation phase and the MD expansion phase an **IVRS call** must be performed if the subject is withdrawn.

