#### **6.5 Subject replacement**

Subjects who drop out or are withdrawn before completion of trial Day 29 in the SD phase and trial Day 57 in the MD dose-escalation and expansion phases, should be replaced. For the SD and MD dose-escalation phases replacement must occur to the same dose cohort as well as the same treatment.

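### Sections 6.4 and 6.5 call for same-dose, same-treatment replacement of subjects withdrawn for a DLT, against the ≥2 row of Table 5-2, and no rule holds undosed subjects at that level

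*Protocol*

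**What the plan says.** **Stagger.** For the single-dose (SD) phase, section 5.2 states that "there will be a time interval of at least 24 hours between dosing of all subjects in each dose cohort", with 24 hours of on-site monitoring. In the multiple-dose (MD) escalation phase, all four subjects of a cohort may be dosed on one day.

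**Toxicity rule.** Table 5-2 counts subjects with related grade 3 toxicity. With one affected of four, the instruction is: "Enter four subjects (3+1) at the same dose level as the current level where the toxicity event occurred". With two or more it is: "The dose-escalation will be stopped at this level, and no further increase of dose will occur". Four further subjects may then be added, but only "at one or maximally two different dose levels between the current dose limiting level and the previous dose level".

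**Safety review.** The criteria in section 5.4 govern the start of the next dose level. The SD criterion is "Safety assessments and evaluations by the Study Safety Group through trial Day 15 for individual subjects in the current dose cohort".

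**Withdrawal.** Under the sentence on who must be withdrawn, section 6.4 lists "Drug limiting toxicity (DLT) or other serious or significant adverse event that warrants discontinuation in the opinion of the investigator".

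**Replacement.** Section 6.5 covers "Subjects who drop out or are withdrawn before completion of trial Day 29 in the SD phase", and before Day 57 in the MD phases, and says they should be replaced. It adds: "For the SD and MD dose-escalation phases replacement must occur to the same dose cohort as well as the same treatment". No exception is given.

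**Cap.** The Summary and section 12.6.1 limit a dose level to 8 subjects.

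**The concern.** Table 5-2 treats a level with two DLTs as dose limiting and directs any further subjects to lower doses. Sections 6.4 and 6.5, followed as written, direct new subjects back to that level. Because replacement is to the same treatment, a replacement for an active subject is also active. Site staff and the Study Safety Group would hold two instructions that disagree, with no statement of which prevails. The text also does not say whether a replaced subject stays in the DLT count.

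The second gap is smaller. Staggered dosing lets the site see a reaction before the next subject is dosed, but the ≥2 row speaks only of dose increases. Whether the remaining subjects of an SD cohort are dosed after a second DLT is left to judgement.

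At stake is avoidable exposure at a dose that the protocol's own count has made dose limiting, in a first-in-human trial that aims to expose as few subjects as possible (section 17.1).

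**Working it through.** The protocol states no figure on this point, so there is none to reproduce. The check has three parts.

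**1. The rules side by side, after two active subjects in a first cohort have had a DLT**

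| Place | What follows |
|---|---|
| Table 5-2, ≥2 row | No dose increase; additions only at intermediate levels; silent on undosed subjects |
| 6.4 | DLT listed under mandatory withdrawal |
| 6.5 | If withdrawn before Day 29 (SD) or Day 57 (MD): replace, same cohort, same treatment |
| Cap | 4 treated + 2 replacements = 6, below 8, so not prevented |

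In an SD cohort where the first two subjects dosed both have a DLT, the text leaves room for four more at that level: the remaining 1 active and 1 placebo, and 2 active replacements. The total is 2 + 2 + 2 = 6.

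**2. Consequence of two active replacements**

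Assume a chance q of a DLT per active subject and none on placebo.

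- Chance of two or more DLTs among 3 active: 3q²(1 − q) + q³
- Expected further DLTs in 2 replacements: 2q
- Chance of at least one: 1 − (1 − q)²

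| q | ≥2 of 3 active | Expected DLTs in 2 replacements | At least one |
|---|---|---|---|
| 10% | 0.028 | 0.20 | 0.19 |
| 20% | 0.104 | 0.40 | 0.36 |
| 33% | 0.255 | 0.66 | 0.55 |
| 50% | 0.500 | 1.00 | 0.75 |

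The last two columns apply only if both subjects are replaced.

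**3. Consequence of the missing SD hold, replacements left out**

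Let v be the chance that an active subject has a DLT that shows before the next dose. All visible means v = q; half visible means v = q/2.

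- First cohort: one active subject is still undosed if the first two active subjects both have a visible DLT, so the expected number is v².
- Repeat cohort: entered after exactly one DLT in the first cohort, with chance 3q(1 − q)². One more DLT then makes two at the level. The expected number of active subjects still undosed is 2v + v(1 − v) = 3v − v².
- Sum per level: v² + 3q(1 − q)²(3v − v²). The two paths exclude each other.

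At q = 20%, all visible: 0.04 + 0.384 × 0.56 = 0.255. Half visible: 0.01 + 0.384 × 0.29 = 0.121.

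| q | All visible | Half visible |
|---|---|---|
| 5% | 0.02 | 0.01 |
| 10% | 0.08 | 0.04 |
| 20% | 0.26 | 0.12 |
| 33% | 0.50 | 0.24 |
| 50% | 0.72 | 0.32 |

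These are expected active subjects per dose level who would be dosed after the count had reached two.

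**The case against.** The best defence is that Table 5-2 already settles the matter. Its ≥2 row has no denominator, unlike the rows for one of four and one of eight, so it need not wait for a full cohort. By offering additions only at intermediate levels, it implies that nobody else enters at the limiting one. The replacement route can also be doubted. The closing words of the 6.4 item, on the investigator's opinion, may qualify the DLT as well. After a single dose there is no treatment left to discontinue. Section 6.5 says should, and the must in section 10.1 is about drop-outs. Safeguards exist: one site runs the SD phase, each subject is watched for 24 hours, an internal committee performs ongoing surveillance, and section 19 lets the investigator or sponsor stop part of the trial at any time. The Study Safety Group also works under a sponsor procedure that is not shown.

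Much of this stands. It makes continued dosing at a limiting level less likely, and at low DLT rates the numbers are small. It does not supply the missing exception in 6.5, and an implication in one table is a weak answer to a replacement instruction elsewhere. The remark about a single dose does not help in the MD escalation phase, where a DLT can end treatment early. Discretion to stop is not a hold.

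A reader might infer that the protocol requires dosing to continue after two DLTs. It does not: it leaves the question open. A reader might also see a DLT defect in the sum 4 + 1 + 4 = 9 against the cap of 8, where one replaced subject is followed by a repeat cohort. That sum arises from a replacement for any reason, so it is a general bookkeeping conflict and gives no support here.

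**Conclusion.** The point holds as a conflict between stated rules, with a smaller gap beside it. Sections 6.4 and 6.5 together call for same-dose, same-treatment replacement of subjects withdrawn for a DLT, while the ≥2 row of Table 5-2 sends new subjects only to intermediate levels. In a first cohort the cap does not decide between them (6 of 8). Separately, no sentence holds undosed SD subjects once two at a level have a DLT.

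The size is illustrative, because the protocol gives no DLT rate. The missing hold is worth 0.01 to 0.08 active subjects per level at rates of 5% to 10%, and 0.12 to 0.72 at rates of 20% to 50%. Two replacements would carry 0.2 to 1.0 expected DLTs at rates of 10% to 50%. These figures assume no DLTs on placebo and independence between subjects. The hold figures further depend on how many DLTs appear before the next dose, which may be only a day later, while the suggested half-life is 15 to 20 days. Later DLTs would escape a hold but would still meet the replacement rule if the subject were withdrawn before Day 29 or Day 57. This should be amended; it does not make the escalation scheme as a whole unsound.

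**What to change.** - **Section 6.5 (and 10.1 to match):** state that subjects withdrawn for a DLT are not replaced and remain in the DLT count for their level.
- **Table 5-2:** state that the count applies as events accrue, and that once two subjects at a level have a DLT nobody else is dosed at that level until the Study Safety Group has reviewed the data.

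The cost is a few sentences in an amendment, with no added subjects, visits or samples. Some later PK and efficacy data are lost where a DLT subject is not replaced, and a hold may cause a short delay. In the SD phase there is room for that. Levels start 5 weeks apart (Table 5-1), so the next level opens on day 36. With one-day gaps the fourth subject is dosed on day 4 and reaches trial Day 15 on day 18, which leaves 36 − 18 = 18 days. This uses the Day 15 basis in sections 5.2, 5.4, 12.6.1 and 17.3. If the Week 5 wording in section 18 governed, the fourth subject's Day 29 would fall on day 32 and leave 4 days.
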